### Intervention fidelity and contamination

The principal investigator will be responsible for monitoring the procedure of the whole study. The intervention logbook will be used by participating nurses to record the number, duration, and administration date of face-to-face sessions and follow-up phone call sessions. To ensure that the delivery of motivational interviewing is consistent with its principals, all motivational interviewing sessions will be audiotaped if permitted by the participant. A random 20% sample will be reviewed using Motivational Interviewing Treatment Integrity Coding Manual 4.2.1 [64] by the local motivational interviewing nurse expert throughout the duration of the intervention. The principal investigator will meet with intervention nurses to discuss the experiences and difficulties to deliver the intervention sessions and provide feedback weekly. Intervention logbooks will also be examined weekly by the principal investigator and further training for nurses will be considered if the delivery of the intervention is not per protocol.

Contamination may occur whereby participants in the control group also receive usual care from trained nurses or interact with participants in the intervention group. However, it is expected that the current study has a low risk of contamination because (1) patients with chronic diseases predominately receive medication management by GPs in China, the involvement of community nurses in medication treatment and consultation is rare, (2) the multifaceted interventions with individualised cognitive behaviour component cannot easily be transferred from one participant to another. Also, the following strategies will be introduced to minimise contamination. First, participants and nurses will be provided with clear information on the nature and purpose of the study. Second, researchers will ask participants not to share information with other participants and keep the education materials to themselves until the end of the study. Finally, only intervention nurses will receive training to deliver the intervention and they will be requested not to discuss the intervention with their colleagues who might be involved in the control group. At the end of the trial, participants in the control arm will be asked whether they have received any information or education on their medications, causal average effect analysis will be considered if high degree contamination occurs [65].

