### Participants

The participants of the trial are community-dwelling older patients with multimorbidity. Multimorbidity is defined using a cut-off of three or more chronic conditions as patients with at least three conditions are more likely to have complex needs and great utilisation of healthcare services [30]. In order to avoid ceiling effect and improve study power to detect changes in adherence, only participants with low medication adherence are considered eligible for the trial. Participants’ inclusion criteria are (1) 60 years old or over, (2) having at least 3 of the 38 chronic conditions (the list of chronic conditions is available at Additional file 1), (3) having at least one medication prescribed for a chronic condition over at least the 3 months prior to inclusion in the study, (4) nonadherence to medications, as defined by scoring 19 or lower on the 5-item Medication Adherence Report Scale (MARS-5) [31], (5) independently managing their medications (i.e., not rely on a carer), (6) able to speak and understand Chinese, (7) able and willing to receive phone calls, and (8) capable of providing a written informed consent to participate in the study.

Exclusion criteria are (1) having a life expectancy of less than 12 months, (2) being institutionalised in a nursing home or in a long-term care facility, (3) planning to move away from the community in the next 6 months, (4) cognitive impairment (Mini-cog scores < 4), and (5) currently participating in research involving chronic disease management. Patients with cognitive impairment are excluded because they may not be able to provide valid answers to the questionnaires.

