### Sample size estimation

Sample size calculation was performed using G*Power Version 3.1.9.4 [32]. Estimation is based upon the primary outcome, medication adherence, at 3 months of follow-up between the intervention and control group. Medication adherence is calculated as sum of the scores from each item using MARS-5. Based on our recent systematic review and meta-analysis on medication adherence interventions among older patients with multimorbidity (manuscript in preparation), a medium Cohen’s effect size (d) of 0.52 on medication adherence is estimated for a medication self-management intervention program. The required sample size will be 120 participants (60 in the intervention group and 60 in the control group) to attain an 80% power with a two-sided α of 0.05. Based on previous studies on older patients with multimorbidity, the attrition rate ranged from approximately 0% [20] to 12% [33]. Therefore, allowing for a 12% attrition rate, the final sample size required is 136 participants. If only 60% of participants agree to participate in the study, 227 participants need to be invited.

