**2nd face-to-face education session**		
• To help patients change negative attitudes and beliefs about medication treatments and become motivated to it. • To help patients change negative perceptions of social norms for medication-taking and facilitate a positive attitude toward social support for adherence	(1) Empower patients with knowledge about the importance of medication adherence and the consequences of nonadherence. (2) Explore patients perceived social norms of adherence and the role of social support networks in supporting medication treatments and self-care. (3) Encourage patients to express their feelings and barriers to their family members and seek help where appropriate. (4) Provide a list of local resource information to patients (e.g., medical care institutions, psychological support organisations, and peer support teams).	❖ Motivational interviewing ❖ Mobilising social support

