### Randomisation, allocation concealment and blinding

Participants per CHC will be randomly allocated to either the intervention or control group. Block randomisation stratified by site with a block size of six will be used to ensure an equal number of participants in the intervention and control group in each CHC. The randomisation and group assignment will be conducted by an independent research assistant (a nurse with a master’s degree) who is not involved in study design and intervention delivery. The randomisation sequence will be generated by using the website Randomization.com (http://www.randomization.com). After completion of baseline data collection, the research assistant blinded to the allocation order will assign the treatment group using sealed opaque envelopes based on the order of recruitment and inform participants of the study group to which they have been assigned. The intervention nurse will receive names and contact details of the participants allocated in the intervention group. This study is single-blinded. Nurses and participants are not feasible to be blinded to the group allocation because of the nature of the intervention. The researcher collecting baseline and follow-up data will be kept blind to participant allocation.

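### Two members of one household can be allocated to opposite arms, which leaves open a route of contamination that may dilute the three-month MARS-5 difference; the size is unknown and probably small

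*Protocol article*

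**What the plan says.** All references are to the protocol article.

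- **Unit of allocation.** Trial design sets randomisation at participant level. Under Randomisation, allocation concealment and blinding, "Participants per CHC will be randomly allocated to either the intervention or control group", in blocks of six stratified by site only.
- **Eligibility and recruitment.** Participants lists eight inclusion and five exclusion criteria, and none mentions household. The only criterion on taking part in research excludes a person who is "currently participating in research involving chronic disease management". That concerns the person's own participation, not a relative's. Recruitment has nurses approach people in the centres' waiting rooms.
- **Family content of the intervention.** Intervention group includes drawing on family and social networks to support self-care. In Table 1, the second face-to-face session has nurses do the following: "Encourage patients to express their feelings and barriers to their family members and seek help where appropriate". After the last face-to-face session the patient receives written material on each of their usual medicines and on medication skills.
- **Contamination.** Intervention fidelity and contamination names contact between control and intervention participants as a possible route. It argues that individualised content does not pass easily from one participant to another. It adds that "researchers will ask participants not to share information with other participants and keep the education materials to themselves until the end of the study". At the end, control participants are asked about any medication information or education they received, and a causal average effect analysis is to be considered if contamination is high.

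**The concern.** Older couples may well use the same health centre, and nothing listed stops both partners from enrolling and receiving different allocations. The intervention patient is then encouraged to seek help at home, from someone who may be a control participant, and is also asked to share nothing with other participants. What passes between the two would move the control member toward the intervention condition and shrink the contrast the trial is built to detect.

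The planned check would not reveal this. Control group describes general practitioners giving consultations and education on medicines as part of usual care. A control participant who answers yes to the end-of-trial question may be reporting that education or something heard from a spouse, and the two cannot be separated.

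At stake is power and the size of the estimate at T2. The design has little slack: 60 per arm gives only just over 80% power.

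**Working it through.** **1. Reproduce the planned size.** The inputs from Sample size estimation are "a medium Cohen’s effect size (d) of 0.52 on medication adherence is estimated" and a sample chosen "to attain an 80% power with a two-sided α of 0.05". The two-sided two-sample t-test (noncentral t) needs 60 per arm and gives power of 80.6%, matching the stated 120. For attrition, 120/(1 − 0.12) = 136.4, against the text: "allowing for a 12% attrition rate, the final sample size required is 136 participants". The plan's figures stand.

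**2. Share of controls living with an intervention participant.** Let q be the share of participants enrolled as couples and p the probability that a couple is split. There are 136q/2 couples, of which a fraction p are split, and each split couple contains one control. Dividing by the 68 controls gives c = q × p.

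- Allocations in unrelated blocks: p = 1/2.
- Consecutive recruits at one centre: they fall in the same block of six with probability 5/6 and then split with probability 3/5; otherwise they split with probability 1/2. So p = 5/6 × 3/5 + 1/6 × 1/2 = 0.583.

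With p = 0.583, q = 5%, 10% or 20% gives about 2, 4 or 8 of 68 controls (3%, 6% or 12%).

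**3. Dilution and power.** Let f be the fraction of the intervention effect that reaches the control member. The diluted effect is d = 0.52 × (1 − c × f). Power is from the two-sided t-test at 60 per arm. The documents give neither q nor f, so both are assumptions.

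| q | f | d (p = 0.5) | Power (p = 0.5) | d (p = 0.583) | Power (p = 0.583) |
|---|---|---|---|---|---|
| none | – | 0.520 | 80.6% | 0.520 | 80.6% |
| 5% | half | 0.514 | 79.7% | 0.512 | 79.5% |
| 5% | full | 0.507 | 78.7% | 0.505 | 78.3% |
| 10% | half | 0.507 | 78.7% | 0.505 | 78.3% |
| 10% | full | 0.494 | 76.5% | 0.490 | 75.8% |
| 20% | half | 0.494 | 76.5% | 0.490 | 75.8% |
| 20% | full | 0.468 | 72.0% | 0.459 | 70.4% |

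Example (q = 10%, f = half, p = 0.583): c = 0.0583, so d = 0.52 × (1 − 0.0583 × 0.5) = 0.505.

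The table isolates dilution. It uses the plan's own t-test basis, not the repeated-measures model of Statistical analysis, and leaves out within-couple correlation.

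**The case against.** The other side has a good deal to say.

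- **The two instructions are not contradictory.** A reader might infer that a split couple cannot follow both. The text does not support that. The second session asks patients to voice their own difficulties and seek help; it does not ask them to teach a relative or hand over session content. There is tension, not impossibility. This stands.
- **The control member does not receive the intervention by design.** A reader might infer this too. The intervention is individual nurse sessions with assessment, motivational interviewing, skills and goals, and the written information on medicines concerns the recipient's own regimen. A spouse gets none of the sessions. Full transfer is therefore an outer bound, not an expectation. This stands.
- **The protocol addresses contact between participants.** Its argument is worded generally, so relatives fall within it, and it plans a check. It is right to credit this. But the argument never weighs people who share a home, and the check cannot identify the source.
- **Eligible couples may be few.** Both must be 60 or over, have at least three listed conditions, score 19 or lower on MARS-5, manage their own medicines, pass the cognitive screen and consent. This stands, and it is why low values of q deserve most weight.
- **Dilution cannot create a false positive.** Correct: it pulls toward no difference. Nor does the dependence between partners simply add harm, since positive correlation within a split couple would lower the variance of the arm difference.
- **This is a condensed article.** The full protocol may hold a household rule. That is possible, and it is another reason for a mild grading.

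**Conclusion.** The gap is real: as published, nothing prevents members of one household from being allocated to opposite arms, and the contamination safeguards do not deal with that case. Part of the intervention can carry over to the control member and may bias the T2 MARS-5 difference toward zero.

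It would go too far to say that the contrast *is* diluted, because the documents give neither the number of couples nor the amount of transfer. With 5-10% of participants in couples and half transfer, the loss is about 1 to 2 percentage points of power. A fall to 70-72% needs both 20% in couples and complete transfer. The effect is probably small, and its direction is conservative. I would class this as a point to consider: a low-cost improvement, not a threat to the trial's validity.

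**What to change.** Add one exclusion criterion under Participants: another member of the same household is already enrolled in this trial. Screen for it with one question at the eligibility appointment described under Recruitment. This closes the household route and removes the tension between the second session and the no-sharing request for couples.

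The cost is one line, one question and the loss of a few otherwise eligible spouses. That loss is minor against the 100 to 300 patient visits per centre per day given under Study setting. The rule has to be in place before enrolment, because a split couple cannot be undone after randomisation. Trial status says recruitment had not begun when the article was submitted.

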**Methods:**

The study protocol follows the recommendations of the Standard Protocol Items: Recommendations for Interventional Trials 2013 statement. This study is a multicentre, single-blind, two-arm randomised controlled trial. Older patients with multimorbidity will be recruited from three community health centres in Changsha, China. A total of 136 participants will be randomly allocated to receive usual care or usual care plus the medication self-management intervention. The intervention will be delivered by community nurses. The 6-week intervention includes three face-to-face education sessions and two weekly follow-up phone calls. Participants in the control group continue to receive all respects of usual care offered by community healthcare providers, including chronic disease management, drug prescription, referral to hospital specialists, health education and consultations regarding patients’ diseases and treatments during centre visits. The primary outcome is medication adherence as measured by the 5-item Medication Adherence Report Scale. Secondary outcomes include medication self-management capacity (medication knowledge, medication beliefs, medication social support, medication skills, and medication self-efficacy), treatment experiences (medication treatment satisfaction and treatment burden), quality of life, and utilisation of healthcare services. All outcomes will be measured at baseline, immediately post-intervention, and at 3-month post-intervention.

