### Control group

Participants in the control group will continue to receive usual care from community GPs, nurses, public health physicians, pharmacists, and other healthcare providers in the CHC under the regular healthcare system of China. In China, community GPs are the primary providers and coordinators of care for patients with chronic conditions. GPs provide patients consultations and education regarding their diseases and treatments (typically clinician-centred) at each patient visit to the chronic disease clinic. Referral to hospital specialists will be made by GPs as needed. For patients diagnosed with hypertension and/or diabetes, community GPs are required to provide scheduled follow-up via home visits or telephone contact at least four times once a year. Community nurses and other healthcare providers assist GPs with chronic disease management.

In respect of medication management, community GPs will prescribe medication regimens, provide medication consultations (including instructions on the medications’ dosage, methods, and frequency), and adjust regimens where appropriate through discussion with patients. Community nurses’ involvement in medication management for patients with chronic conditions is comparatively little. No structural medication self-management education session will be provided for patients in usual care group.

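### The end-of-trial contamination question cannot tell contamination from usual care, because controls receive medication information and education by design

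*Protocol article*

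**What the plan says.** The section on intervention fidelity and contamination names two routes: "Contamination may occur whereby participants in the control group also receive usual care from trained nurses or interact with participants in the intervention group". It gives reasons for expecting low risk and lists preventive measures. The one check it describes comes at the end of the trial, when "participants in the control arm will be asked whether they have received any information or education on their medications". No source, content or period is attached to the question. The use of the answer follows directly: "causal average effect analysis will be considered if high degree contamination occurs". No level is given for a high degree.

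Usual care is described in two places. Under Control group, "GPs provide patients consultations and education regarding their diseases and treatments (typically clinician-centred) at each patient visit to the chronic disease clinic"; GPs also give medication consultations that cover dose, method and frequency. The abstract lists "health education and consultations regarding patients’ diseases and treatments during centre visits" as part of control-group care. What controls do not get is also stated: "No structural medication self-management education session will be provided for patients in usual care group".

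Receipt in the intervention arm is recorded in a nurse logbook. The Statistical analysis section commits primary and secondary outcomes to intention to treat.

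**The concern.** The definition of contamination and the question meant to detect it do not match. The definition concerns exposure to the trial's intervention through a trained nurse or another participant. The question concerns any medication information from anyone, which usual care is meant to supply. A control who had ordinary GP care and nothing else would truthfully answer yes.

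Two things are at stake. First, a substantial yes rate could not be interpreted, although contamination is a recognised risk when individuals are randomised within a health centre. Second, the answer informs a decision about a further analysis, and it could distort the size of that analysis's estimate if it were used as the receipt variable. Exposure that is not asked about during the trial cannot be recovered afterwards.

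**Working it through.** **1. Text against text.**

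| Exposure of a control | Contamination as the article defines it? | Answer to the question as printed |
|---|---|---|
| GP education or medication instruction only | No | Yes |
| Medication advice from a trained study nurse | Yes | Yes |
| Programme content passed on by an intervention participant | Yes | Probably yes |
| None of these | No | No |

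The first row and the next two cannot be separated. The first row should be common. The eligibility criteria require at least three chronic conditions and a medicine prescribed for at least 3 months. Patients with hypertension or diabetes are due at least four GP follow-ups a year. Over a 6-week intervention plus 3 months (about 4.5 months) that is 4 × 4.5/12 = 1.5 contacts on average, on top of clinic visits.

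**2. The plan's own figures.** The article states no contamination rate, threshold or causal estimate. The one effect size to work from is the planning value d = 0.52 in the sample size section. It reproduces: a two-sided 5% t-test has power 0.7998 with 59 per arm and 0.8065 with 60, so 60 per arm is right. For attrition, 120/0.88 = 136.4, against 136 stated.

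**3. Possible distortion.** Assumptions that are not in the documents:
- the causal analysis is a complier-type ratio, ITT/(pI − pC);
- pI, receipt in the intervention arm, is 0.95;
- pC is the share of controls who answer yes;
- there is no true contamination, so every yes is usual care.

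The correct estimate is then ITT/0.95, which is 1.05 × ITT. The estimate obtained is ITT/(0.95 − pC). Overstatement is the ratio of the two, 0.95/(0.95 − pC).

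| pC | Overstatement | Estimate if ITT = 0.52 SD |
|---|---|---|
| 0 | 1.00 | 0.52/0.95 = 0.55 |
| 0.10 | 0.95/0.85 = 1.12 | 0.52/0.85 = 0.61 |
| 0.30 | 0.95/0.65 = 1.46 | 0.52/0.65 = 0.80 |
| 0.50 | 0.95/0.45 = 2.11 | 0.52/0.45 = 1.16 |
| 0.70 | 0.95/0.25 = 3.80 | 0.52/0.25 = 2.08 |

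A simulation with 60 per arm and full receipt agrees with the formula: medians were 0.65, 1.04 and 2.62 SD at 20%, 50% and 80% yes, against 0.52/(1 − pC) = 0.65, 1.04 and 2.60.

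**4. Does asking controls only matter?** Suppose the same broad question went to both arms and usual care produced yes at rate pC in each. The receipt difference would be pI(1 − pC) and the overstatement 1/(1 − pC). At pC = 0.5 that is 2.00, against 2.11 for controls only. With pI = 0.88 the controls-only figure is 0.88/0.38 = 2.32. With pI = 1 the two are equal. The broad wording is the main cause, and the asymmetry adds little at these values.

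**5. Significance.** Dividing by pI − pC rescales the estimate and its standard error together, so the test statistic is roughly unchanged. The intention-to-treat analysis does not use the question at all.

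**The case against.** The strongest reply is that the article paraphrases an enquiry and does not print an item. It does not say that a yes is scored as contamination or becomes the receipt variable, and the full questionnaire may be narrower. That limits how much can be claimed about size. It does not remove the mismatch: the article states what is asked, of whom and for what decision, and that text conflicts with its own account of usual care.

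Other objections stand, and they rule out several stronger readings that a reader might infer:

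- *The question triggers a replacement for the main result.* The analysis is only to be considered, and intention to treat already governs the primary and secondary outcomes.
- *A null result could be rescued as contamination.* Under the assumed ratio, a null intention-to-treat result stays null.
- *The whole multiplier over ITT is error.* With 95% receipt, the factor 1/0.95 is a legitimate adjustment for non-receipt, so the benchmark is ITT/0.95.
- *Asking controls only unblinds the assessor.* The article does not say who asks. The question comes at the end of the trial, and no effect on masked T2 outcomes is shown.
- *The question is worthless.* A low yes rate would be reassuring. A substantial rate is what cannot be interpreted.

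**Conclusion.** The point holds as a mismatch between the contamination question and the article's own definitions of contamination and usual care. Followed as printed, the question cannot separate the two and could wrongly suggest high contamination.

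The numerical consequence is conditional. The overstatement of about 1.1, 2.1 and 3.8 times at 10%, 50% and 70% yes rests on a complier-type ratio, on this answer being used as receipt, on 95% receipt in the intervention arm and on no true contamination. The documents give none of these, nor any expected yes rate. Only the size of one optional secondary estimate is at risk. The intention-to-treat result is unaffected and significance essentially so. The change is still worth making, because it is cheap and must be in place before the question is asked.

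**What to change.** Replace the broad question with items specific to the intervention:
- a medication session or call with a trained study nurse;
- having seen or received the study's education materials;
- having made an adherence improvement plan;
- having discussed the programme with an intervention participant.

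Ask them after all T2 outcomes have been recorded, so that the answers cannot influence the outcome assessment. Preferably ask both arms, so that the interviewer need not know the allocation. Define receipt in both arms from the same intervention-specific exposure, using the logbook for intervention participants. State that any causal estimate is supplementary to intention to treat and is reported with its assumptions.

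Putting the existing broad question to both arms would not be enough, as step 4 of the working shows. The cost is rewording one item, a sentence of analysis text, and one or two extra minutes per T2 call.
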